# Combination of Shengji ointment and bromelain in the treatment of exposed tendons in diabetic foot ulcers: study protocol for a non-blind, randomized, positive control clinical trial

**DOI:** 10.1186/s12906-023-04128-z

**Published:** 2023-10-10

**Keywords:** Administration, topical, Bromelain, Diabetic foot, Herbal medicine, Medicine, Chinese Traditional, Ointment, Tendon injuries

## Abstract

**Background:**

Diabetic foot ulcers often affect tendon tissue. Consequently, the infection may spread proximally along the tendon, leading to amputation or even the death of patients. Exposed, degenerated, and necrotic tendons are key factors affecting the healing of diabetic foot ulcers. The effective treatment of the tendon involvement may positively affect the prognosis. In clinical practice, treatment with Shengji ointment and bromelain induces islands of granulation tissue on the denatured tendon surface, which gradually grows and merges. Ideally, the exposed tendon is covered entirely by granulation tissue.

This trial aims to assess the effect of a combined treatment regime of Shengji ointment, which has been shown to regenerate muscle tissue and pineapple protease in preventing the loss of function and amputation caused by tendon necrosis. This trial will provide high-quality evidence for the effectiveness of this combination in healing diabetic ulcers with tendon necrosis.

**Methods:**

The sample size will be 180 patients who will be randomly assigned 1:1 to a treatment group (90 patients) using Shengji ointment combined with bromelain and a control group (90 patients) using hydrocolloid dressing. Both groups will continue their conventional treatments, such as blood glucose and blood pressure medication, lipid regulation, antiplatelets, and others. The primary outcome will be the wound coverage with granulation tissue. Secondary outcomes will be the wound healing rate, amputation extent (where needed), time to granulation, and the Maryland Foot Score. Other efficacy outcomes will be the time to debridement of necrotic tendon tissue and granulation tissue score.

**Discussion:**

This study will treat patients with diabetic foot ulcers with exposed, degenerated, and necrotic tendons with Shengji ointment and bromelain. The trial aims to promote regeneration and healing, to preserve the limb and its function, and to develop a comprehensive and effective protocol that can be applied to promote the healing of exposed tendons in diabetic foot wounds.

**Trial registration:**

ChiCTR2000039327; date of registration: 2020-10-23.

**Supplementary Information:**

The online version contains supplementary material available at 10.1186/s12906-023-04128-z.

## Administrative information

Note: the numbers in curly brackets in this protocol refer to SPIRIT checklist item numbers. The order of the items has been modified to group similar items (see http://www.equator-network.org/reporting-guidelines/spirit-2013-statement-defining-standard-protocol-items-for-clinical-trials/).

## Background and rationale {6a}

A diabetic foot is defined as the destruction of skin and deep tissues distal from the ankle joint in patients with diabetes, often combined with infection and/or peripheral arterial occlusive disease of varying degree in the lower limbs and, in severe cases, involving muscle and bone tissue [1]. Diabetic foot is one of the most common and serious chronic complications of diabetes and a frequent cause of disability and death [2]. It is estimated that a limb is amputated every 20 s in patients with diabetes worldwide [3]. Diabetic foot ulcers often extend deep into tissue and the underlying tendons, and the infection can spread proximally along the tendon, eventually leading to amputation or death [4]. Exposed, degenerated, and necrotic tendons impair the healing of diabetic foot ulcers [5], and the effective treatment of these tendon injuries improves the prognosis of wound healing [6].

The *International Diabetic Foot Working Group* guidelines emphasize that the management of diabetic foot ulcers requires a multidisciplinary and comprehensive approach [7]. In clinical Traditional Chinese Medicine practice, denatured but still vital tendon surfaces are covered with patches of new granulation tissue that gradually grow and eventually merge with each other when treating diabetic ulcers with a combination of Shengji ointment and bromelain [8].

In Traditional Chinese Medicine (TCM), treatment according to the method of Hua Fu Sheng Ji entails bromelain, which targets liquefied necrotic tendon and fascia, removes necrotic tissue, and prevents further putrefaction, thereby providing a clean wound bed that promotes healing in diabetic ulcers [9]. The combination of bromelain with Shengji ointment uses the synergistic effects of the substances and promotes the in situ regeneration of granulation tissue and epithelial tissue. It has been shown that the content of total protein, total amino acid, and lysozyme per unit of wound exudate increases significantly over different periods of time under this treatment, providing the nutrients for wound healing [10]. This may result in a reversal of the denaturation of the tendon tissue and stimulates the growth of granulation tissue that starts to cover tendon tissue, which may allow to retain parts of the tendon and to preserve foot function to a certain extent.

Previous animal studies [11] have shown that the application of bromelain combined with Shengji ointment can target and remove necrotic tendon tissue, promote tissue regeneration, and realize tissue repair in situ. The healing rate was 60%, and the efficacy rate was 94.3%. By changing the pH-value and lysozyme content of the wound, the method may liquefy the necrotic tendon and fascia, control infection, and stop decay. The TCM ointment Shengji mainly focuses on the growth of muscle and skin by providing amino acids, proteins, and other substances needed for wound repair and stimulating epidermal growth. The combination of Shengji with bromelain can accelerate tissue growth and promote wound healing. Our preliminary research [National Natural Science Foundation Project (30873270): Mechanism Research on the Effect of Decomposing Rot and Promoting Muscle Growth on Diabetic Foot Tendon Necrosis [12] has found that some degenerated tendon tissue recovered after treatment, and granulation tissue grew to cover the tendon tissue, retaining parts of the tendons and preserving foot function to a certain extent, which we called the “Jin Zhi Xue Hua” phenomenon. Later, based on further research [National Natural Science Fund Project (81573972) [13], we found that the creation of a steady-state microenvironment promoted the perfusion of tendons during the healing of diabetic foot ulcers] and concluded that “the method of Hua Fu Sheng Ji can promote a stable microenvironment in diabetic foot ulcers.” It is of great significance to explore the underlying mechanisms to improve diabetic foot ulcer repair and to enrich the theory of topical treatment in TCM.

This clinical trial will follow a multicenter, randomized, positive control design aimed at assessing the combination treatment’s efficacy in promoting tendon healing and preserving both the limb and its function in patients with Wagner grade 3–4 diabetic foot ulcers and tendon exposure.

The trial aimed to (a) investigate the effect of Shengji ointment and pineapple protease, used for muscle regeneration and healing, as therapeutic drugs in preventing amputation necessitated by tendon degeneration and necrosis, thereby preserve limb function, and to (b) develop high-quality evidence and a comprehensively effective plan for promoting the healing of exposed tendons in diabetic foot ulcers.

### Objectives {7}

The objectives of this trial are as follows:

Create high-quality evidence on the effects of the treatment of diabetic ulcers with a combination of Shengji ointment;Evaluate the efficacy and safety of the combination treatment;Develop a generalizable TCM treatment plan for diabetic foot ulcers with tendon exposure.

### Trial design {8}

This study was a multicenter, non-blind, randomized, positive control trial.

## Methods: participants, interventions, and outcomes

### Study setting {9}

The diagnostic criteria for diabetic foot refer to.The Technical Guiding Principles for Clinical Research of New Traditional Chinese Medicine for Diabetic Foot (Draft for Soliciting Opinions [14]) and the Guidelines for Diagnosis and Treatment of Diabetic Foot in China (2019 Edition) [15] issued by the Drug Evaluation Center of the State Drug Administration;Diabetic foot grading standard: Wagner grading.

### Eligibility criteria {10}

#### Inclusion criteria

Patients who meet the following criteria will be included:

Diagnostic criteria for diabetic foot disease and Wagner grade 3–4 ulcers with exposed tendon tissue;Age between 18 and 85 years;Fasting blood glucose ≤ 10 mmol/L;Targeted ulcer debridement area between 1 and 20 cm^2^ (for patients with multiple lesions, the largest ulcer will be the target lesion);An ankle-brachial index ≥ 0.5 on the side of the limb with the ulcer;The ulcer has blood, pus, or sticky secretion;Voluntary participation and signing of an informed consent form.

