##### Treatment 2: Pineapple protease (bromelain)

Specification: 10,000 units.Formulation: Tablet.Dosage: For external use. It will be applied to exposed tendons and areas with necrotic tissue.Route of administration: Topical.Frequency of administration: Once every 24 h.Treatment course: Four weeks.Manufacturer: Shantou Olive Pharmaceutical Co., Ltd., Shantou City, Guangdong, China.

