### Outcomes {12}

#### Primary outcome

The wound coverage with granulation tissue will be the primary outcome. The development of granulation tissue will be assessed as follows:

$$\text{Wound coverage rate} = \text{The wound area covered by granulation tissue}\, (\text{mm}^{2})/\text{Whole wound area}\, (\text{mm}^{2}) \times 100\%$$

We will use three-dimensional scanning to obtain the wound surface topography and the inSight® platform (eKare, Inc., Fairfax, VA, USA) to identify the different tissue types and to measure the areas covered by them.

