#### Other indicators of treatment efficacy

We will also record the following parameters:

Clearance time (days): The period from enrollment (day 0) to the complete clearance of degenerated and necrotic tendon tissue.

Granulation tissue score: Evaluation of scores at enrollment (day 0), visit 2 (week 2), and at the end of the trial (week 4).

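### The target lesion is chosen by size alone, so a patient with several ulcers can be scored on one without exposed tendon

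*Protocol article*

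**What the plan says.** All quotes are from the protocol article. Under Eligibility criteria {10}, Inclusion criteria, the first item describes the patient's disease: "Wagner grade 3–4 ulcers with exposed tendon tissue". A later item limits the wound to be followed, "Targeted ulcer debridement area between 1 and 20 cm^2", and adds in brackets: "for patients with multiple lesions, the largest ulcer will be the target lesion". Another item says of an unspecified ulcer: "The ulcer has blood, pus, or sticky secretion".

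Under Primary outcome: "The wound coverage with granulation tissue will be the primary outcome". It is computed as granulated area divided by the area of the whole wound. Tendon is not mentioned, and neither is the target lesion.

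Two other places presuppose tendon in the wound. On bromelain, the section Treatment 2 says: "It will be applied to exposed tendons and areas with necrotic tissue". Under Other indicators of treatment efficacy, clearance time ends at "complete clearance of degenerated and necrotic tendon tissue".

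Sequence generation {16a} uses ulcer location as a minimisation factor. The ankle-brachial index criterion refers to the limb that carries the ulcer. Neither says which ulcer is meant when there are several.

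**The concern.** Exposed tendon with Wagner grade 3–4 is a condition on the patient, whereas the target lesion is a property of one wound and is picked by area. The two coincide when there is a single ulcer. With several ulcers they can separate, and the text has nothing to bring them back together.

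What is at stake is what the primary comparison measures. The title, the rationale and the discussion all ask whether the combination helps granulation tissue cover exposed tendon. Coverage of a wound without exposed tendon answers a different question. Four hospitals apply the rule, so an unclear rule may also be applied in different ways.

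**Working it through.** The protocol gives no figure for this point, so the main check is to apply the text to a case.

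**Example (invented).** A patient has ulcer A, 4 cm², Wagner grade 3 with exposed tendon, and ulcer B, 12 cm², superficial, without exposed tendon.

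1. Disease criterion: met, because ulcer A is present.
2. Target lesion: 12 > 4, so ulcer B.
3. Area criterion on the target: 1 ≤ 12 ≤ 20, met.
4. Primary outcome: granulated area of B divided by whole area of B. It can be computed, but it contains no exposed tendon.
5. Clearance time: B has no tendon tissue to clear, so the event is undefined.
6. Ulcer location for minimisation: if it follows the target, it is the location of B.
7. Ankle-brachial index: the choice of ulcer matters only if A and B are on opposite limbs.

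Steps 4 to 6 assume that outcomes and location are taken on the target lesion. The protocol does not say so outright. It follows from the purpose of naming a target, and no other rule says which wound to measure.

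**Possible size (illustration only).** Let f be the share of patients whose target has no exposed tendon, δ the treatment difference in tendon ulcers and δ₀ the difference in the other ulcers. The expected difference is

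δ_obs = (1 − f)·δ + f·δ₀.

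The documents give neither f nor δ₀. Sample size {14} expects effectiveness of 50% and 71%, so take δ = 71 − 50 = 21 points. Assume f between 5% and 15%, that is 0.05 × 180 = 9 to 0.15 × 180 = 27 patients.

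| δ₀ assumed | f = 5% | f = 15% |
|---|---|---|
| 0 (no effect without tendon) | 0.95 × 21 = 19.95 | 0.85 × 21 = 17.85 |
| 10.5 (half the effect) | 19.95 + 0.05 × 10.5 = 20.475 | 17.85 + 0.15 × 10.5 = 19.425 |
| 21 (same effect) | 21 | 21 |

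Under these assumptions the loss runs from nothing to about 3 points (21 − 17.85 = 3.15). I do not convert it to power: the sample size section states no power and does not tie its effectiveness rates to the coverage outcome.

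**The case against.** The best defence is that the list is cumulative. Its first item describes the study ulcers, and later mentions of a lesion or ulcer can be taken to refer back to them, so that the largest ulcer means the largest qualifying one. The rest of the article treats the studied wound as the tendon wound, so this may well be the intent. The point stands as far as intent goes. The sentence does not say it, however, and a site that follows it literally makes no error.

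Standard operating procedures and a trial-specific case report form are mentioned but not shown, and either could settle the matter. Yet the selection rule is stated in this article, and as stated it is loose.

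Several stronger readings are tempting and are not supported:

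- **That treatment cannot work in the other ulcers.** Intervention description {11a} and Treatment 2 also direct bromelain to necrotic tissue, Shengji ointment covers the wound, and the background credits the combination with promoting granulation and epithelial tissue generally. A zero effect is an assumption.
- **That a known share of patients is affected.** The documents give no frequency of multiple ulcers, still less of those whose largest ulcer lacks exposed tendon.
- **That the rule biases the comparison.** It is the same in both arms and rests on a baseline feature. It can blur the contrast but does not by itself favour an arm.
- **That patients are wrongly excluded when a larger ulcer without exposed tendon exceeds 20 cm².** A cap on the largest ulcer may be intended, since amputation and the Maryland Foot Score concern the limb or foot and another large wound could affect them.
- **That an important endpoint is lost.** Clearance time is listed among the other indicators, neither primary nor secondary.

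**Conclusion.** The point holds as a fault of wording with a real consequence. Taken literally, the rule allows the primary outcome to be measured on a wound without the condition under study, and clearance time is then undefined. It can arise only in patients with several ulcers whose largest has no exposed tendon.

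The number of such patients is unknown, and the dilution cannot be derived from the documents. The range of 0 to about 3 points rests on an assumed share of 5–15% and on an effect in the other ulcers anywhere between nil and the full 21 points. The textual fault does not depend on those figures. I rate it a cheap improvement of moderate to minor weight, not a fault that must be corrected before the trial can be relied on.

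**What to change.** Reword the bracketed rule along these lines: for a patient with more than one ulcer, the target lesion is the largest ulcer that itself has exposed tendon and is Wagner grade 3–4. Add that the wound outcomes, the side used for the ankle-brachial index and the ulcer-location minimisation factor all refer to that lesion.

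Treat any size limit on other, untargeted ulcers as a separate decision for the sponsor. Once the target is tied to tendon exposure, the 1–20 cm² limit no longer restrains a larger ulcer elsewhere. Whether such patients belong in the trial is a question about the population and should be answered explicitly.

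Trial status expected recruitment to end in December 2022, before the article appeared in October 2023. If enrolment has closed, use baseline records to identify, before analysis, any patient whose target had no exposed tendon, and add a sensitivity analysis of the primary outcome without them. Because the criterion is a baseline feature, leaving these patients out in both arms keeps the comparison like with like.

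The cost is one sentence, a matching case report form instruction and, if needed, one extra analysis. The sample size does not change. The small downside is that in a few patients the scored wound will not be their largest.

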#### Exclusion criteria

Patients who meet any of the following criteria will be excluded:

Skin ulcer caused by electrical, chemical, or radiation injury, tumors, varicose veins, or other reasons; or malignant lesions within the ulcer;Severe clinical infection indicated by cellulitis, fever, elevated white blood cell count, bacterial culture, or increased (high-sensitivity) C-reactive protein levels;Severe uncontrollable hypertension with systolic blood pressure ≥ 160 mmHg or diastolic blood pressure ≥ 110 mmHg;Serum albumin levels < 28 g/L;Hemoglobin < 90 g/L;Platelet count < 50 × 10^9^/L;Severe heart, liver, or kidney injury, in case of medical treatment that may seriously affect the safety and treatment;Pregnancy, family planning, or breastfeeding women;Cognitive dysfunction preventing fully informed consent;Allergic disposition or allergic to the ingredients of the treatment under investigation and reference drugs;Participation in other clinical trials during the past one month;In the judgment of the researcher, inability to complete the trial or comply with its requirements.

### Who will take informed consent {26a}

Before a patient is enrolled in this trial, the researcher is responsible for explaining the purpose, nature, procedure, possible benefits, and risks of their participation to them or their designated representative in written form. Patients shall be informed that they have the right to withdraw from the study at any time. A written informed consent form must be given to each patient before enrollment such that they can confirm that they understand and agree with their participation. Informed consent forms must be voluntarily signed before the patients are enrolled in the trial. The informed consent form will be kept as one of the original materials for the trial.

### Interventions

#### Explanation for the choice of comparators {6b}

As a commonly used dressing for diabetic foot wounds, the hydrocolloid dressings are safe, reliable, effective, and superior in the treatment of diabetic foot ulcers and other chronic difficult-to-treat wounds. The hydrocolloid dressing was determined to be the best comparator as a positive control.

#### Intervention description {11a}

Both the intervention and control groups will receive routine medical and surgical treatment (blood sugar control, blood pressure reduction, lipid regulation, antiplatelet medication, debridement, and others).

In the intervention group, bromelain powder will be applied to the exposed tendon and necrotic tissue, and the wound will be covered with Shengji ointment. In the control group, a hydrocolloid dressing will be used to cover the wound.

##### Treatment 1: Shengji ointment

Size: 30 g/box.Formulation: Ointment.Usage and dosage: For external use. The ointment will be spread on skimmed cotton and applied to the affected area.Route of administration: Topical.Frequency of administration: Once every 24 h.Treatment course: Four weeks.Manufacturer: Tianjin Darentang Jingwanhong Pharmaceutical Co., Ltd, Tianjin, Tianjin, China.

##### Treatment 2: Pineapple protease (bromelain)

Specification: 10,000 units.Formulation: Tablet.Dosage: For external use. It will be applied to exposed tendons and areas with necrotic tissue.Route of administration: Topical.Frequency of administration: Once every 24 h.Treatment course: Four weeks.Manufacturer: Shantou Olive Pharmaceutical Co., Ltd., Shantou City, Guangdong, China.

##### Active control: Comfeel® Plus wound dressing

Size: 25 g/piece.Formulation: Hydrocolloid dressing.Usage and dosage: Apply Comfeel® dressing to the ulcer. Ensure the dressing height is at the level of the surrounding skin. Then, apply a layer of dressing over the ulcer and surrounding area.Manufacturer: Coloplast Group, Humblebaek, Denmark.Route of administration: Topical.Frequency of administration: Once every 24 h.Course of treatment: Four weeks.

#### Criteria for discontinuing or modifying allocated interventions {11b}

In enrolled patients who withdraw from the trial without completing the clinical protocol for any reason during the trial, two conditions will be distinguished: researcher-determined discontinuation and voluntary withdrawal.

##### I. Termination of a patient’s participation based on the researcher’s decision

The researchers may decide to withdraw enrolled subjects from the study when they establish that they are not suitable to continue the study for any of the following reasons:

During the trial, clinical endpoints (such as the need for surgery) are reached.The patient undergoes surgical treatment other than debridement of the ulcer site.During the clinical trial, patients experience complications or physiological changes that make it inappropriate for them to continue to receive treatment within the trial.Use of other prohibited treatments or drugs that affect the assessment of the efficacy and safety of the intervention.If serious adverse events occur during the trial, the researcher may decide whether to suspend the trial.Poor compliance of the patients that results in the failure of 80% of the prescribed dosage of topical drugs (except cured patients) or the failure of 120% of the prescribed dosage.

Subjects who will be withdrawn from the trial will undergo a final visit to evaluate each efficacy indicator and to complete a safety assessment.

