#### Relevant concomitant care permitted or prohibited during the trial {11d}

No additional Chinese or Western drugs related to the treatment of the ulcer (vasodilators, such as lipid microspheres prostaglandin injection, beraprost sodium, cilostazol, sagresol hydrochloride, nefuram, butalbital, and hexaketone cocaine, among others; antiplatelet drugs, such as aspirin and clopidogrel; anti-coagulant drugs, such as unfractionated heparin or low-molecular-weight heparin, and oral anti-coagulants; or TCM or proprietary Chinese medicine, topical antibiotics, trimethoprim/sulfamethoxazole, and others, which have the effect of muscle growth and act as astringents in the treatment of sores) should be used during the trial. The same applies to biological treatments (such as stem cell therapy, topical autologous platelet-rich plasma, maggot therapy, cell growth factors, chymotrypsin, and TCM or Chinese herbal tonics with similar functions as the trial treatment).

Drugs that are required to treat comorbidities may be continued. These drugs must be recorded in detail on the case report form, including the name of the drug, dosage, frequency, and duration of use.

Glucose-lowering drugs (oral antidiabetics and insulin) will be selected according to the patient’s blood glucose level at the time of enrollment and treatment regimen. Except for uncontrolled hyperglycemia, the type of glucose-lowering drug or insulin regimens of patients will remain unchanged, although the dosage will be adjusted according to blood glucose levels. Blood glucose levels and glucose-lowering drug doses will be recorded in a timely and detailed manner on the case report form. Patients whose blood glucose levels cannot be normalized within a week will be discontinued from the trial.

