#### Secondary outcomes

As secondary outcomes, we will determine the wound healing rate, amputation rate and extent, granulation time, and Maryland Foot Score.

Wound healing rate = (Original wound area - unhealed wound area)/Original wound area ×100%.Amputation extent: A extensive amputation refers to an amputation above the ankle, while a limited amputation refers to an amputation below the ankle. The amputation level will be identified in a multidisciplinary team of vascular surgeons and orthopedic foot and diabetes specialists according to the results of the lower limb angiography.Granulation time (days): The period of time within which new granulation tissue appears within the wound.The Maryland Foot Score will be determined to evaluate foot function, including the presence or absence of pain. The maximum score is 100 points, > 89 points indicate excellent function, 75–89 points good function, 50–74 average, and < 50 points poor function.

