### Data collection and management

#### Data management {19}

Research medical records.

Since most outpatient medical records at China’s hospitals are kept by the patients themselves, the case report form will be designed specifically for this trial to preserve first-hand information. The research medical records are the original documents of the trial patients, which are properly kept by each trial center.

2Electronic data management.

The electronic case report form is created using the clinical trial data management system (eCDMS3.0) at Xiyuan Hospital developed by the Chinese Academy of Traditional Chinese Medicine, and the data will be collected and managed online.

Full analysis set: This refers to patients receiving the allocated treatment at least once and having data on at least one post-treatment primary outcome measurement. For patient data that fail to observe the whole treatment process, the data from the last observation will be carried forward to the final last observation carried forward.Per protocol set: Good compliance (80% ≤ treatment compliance ≤ 120%), not taking prohibited medications during the study, and no serious violation of the trial protocol.Safety set: All patients who are randomized and use the trial treatment at least once.

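### Withdrawal for surgery or uncontrolled glucose can end follow-up before day 28, so later amputations may be missed and an early coverage value may stand in for the primary outcome

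*Protocol article*

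**What the plan says.** All places are in the protocol article.

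- **Termination based on the researcher's decision (under {11b}).** The rule is discretionary and concerns the study as a whole: "The researchers may decide to withdraw enrolled subjects from the study when they establish that they are not suitable to continue the study". Two of the listed reasons are surgical: "During the trial, clinical endpoints (such as the need for surgery) are reached" and "The patient undergoes surgical treatment other than debridement of the ulcer site". The same section then provides: "Subjects who will be withdrawn from the trial will undergo a final visit to evaluate each efficacy indicator and to complete a safety assessment". No contact after that visit is stated.
- **Concomitant care {11d}.** This rule is mandatory: "Patients whose blood glucose levels cannot be normalized within a week will be discontinued from the trial".
- **Background and rationale {6a}.** The treatments are to be studied as "therapeutic drugs in preventing amputation necessitated by tendon degeneration and necrosis", and preserving limb function is part of the same aim.
- **Secondary outcomes.** Here "we will determine the wound healing rate, amputation rate and extent, granulation time, and Maryland Foot Score".
- **Participant timeline {13}, Table 1.** Amputation extent is scheduled at days 14 and 28. Wound coverage and the Maryland Foot Score are scheduled at days 0, 14 and 28.
- **Data management {19}.** The full analysis set requires at least one treatment and at least one post-treatment value of the primary outcome. For patients not observed through the whole treatment, "the data from the last observation will be carried forward to the final last observation carried forward".
- **Trial design {8}.** The trial is not blinded.

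**The concern.** Reaching an event that the trial sets out to prevent, and counts as an outcome, is also a reason to stop observing the patient. The text does not separate stopping the allocated treatment from leaving the study. The section on discontinuing interventions is written in terms of study participation, and the glucose rule is written in terms of the trial.

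Two comparisons are exposed. The amputation comparison can miss events between the final visit and day 28. The primary comparison can use, as the day-28 value, a coverage measurement taken when treatment was already failing. The person deciding on withdrawal knows the arm, so the same clinical course could end follow-up in one arm and not in the other.

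**Working it through.** The plan states no figure on this point, so there is none to reproduce. The check follows the stated rules through to the data, then sizes the effect on the primary outcome under stated assumptions.

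**Step 1. What the rules produce for three kinds of patient**

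1. *Non-debridement surgery has been done and the patient is withdrawn.* The final visit evaluates every efficacy indicator, so an amputation that has already taken place can be recorded. A later change of level before day 28, and later foot function, are not covered.
2. *Surgery is needed and the patient is withdrawn before it takes place.* If the final visit precedes the operation, nothing stated collects the amputation or its level. The coverage seen at or before the final visit is carried to day 28.
3. *Glucose is not normalised within a week.* Discontinuation can fall before the day-14 visit. The final-visit sentence stands in the researcher-decision section, and the article does not say whether it also applies here. If a scan is taken, it is carried forward. If none is taken, the patient fails the full-analysis-set definition and leaves the primary analysis. An amputation before day 28 is not covered.

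So there are two routes into the primary analysis, a carried-forward value or exclusion from the set.

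**Step 2. Effect on amputation**

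No surgery or amputation rate is given, so the number of missed events cannot be computed. With 90 patients randomised per arm, each missed amputation lowers that arm's rate by 1/90 = 1.1 percentage points.

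**Step 3. Effect on mean coverage**

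Inputs, all assumed because the documents give none:

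- w_T and w_C, the shares of treated and control patients who are withdrawn for surgery and carried forward;
- L, their mean carried-forward coverage, 20% to 60%.

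Carrying forward contributes w × L to an arm's mean, and scoring surgery as 0% contributes nothing. The treated-minus-control difference under carry-forward therefore departs from the difference under 0% scoring by:

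shift = (w_T − w_C) × L

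| Control | Treated | L = 20% | L = 40% | L = 60% |
|---|---|---|---|---|
| 15% | 5% | −2 | −4 | −6 |
| 5% | 15% | +2 | +4 | +6 |
| 10% | 10% | 0 | 0 | 0 |

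For example, (0.05 − 0.15) × 40 = −4 points of mean coverage. With 90 per arm, a 10-point gap in rates is 0.10 × 90 = 9 patients.

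The sign follows the arm with more surgery. More surgery among controls makes the treatment look worse than under 0% scoring, and more surgery among treated patients makes it look better. The reference of 0% is a convention chosen to show the size, not a known truth.

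**The case against.** The strongest reply is that the text loses less than it seems to.

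- **Withdrawal is permitted, not automatic.** A reader might infer that every patient who needs surgery is removed. The researcher-decision section says only that researchers may decide so. This stands, although in an unblinded trial discretion leaves room for the decision to differ by arm. The glucose rule is different, since it is mandatory.
- **The triggering operation need not be lost.** A reader might infer that the amputation prompting withdrawal goes unrecorded. The final visit covers each efficacy indicator, and Statistical methods {20a} promises a description of withdrawals with time and reason. This stands. The gap is what happens after that visit.
- **The carried value need not predate surgery.** That is an inference. The timing of the final visit relative to surgery is not fixed, so the last scan could come before or after it, or not exist.
- **Scoring surgery as failure is a choice.** Coverage is defined as a tissue measurement, and 0% or worst rank is one of several defensible strategies that would change what is estimated. Such scoring is commonly left to an analysis plan, which is not shown. This stands, so the absence of a scoring rule is not itself the error.
- **The article is condensed.** The full protocol might provide follow-up after withdrawal. That is possible, but leaving the study is what the article states, and carry-forward is stated too. Who is followed, and until when, is protocol content, and an analysis plan cannot recover amputations that were never collected.

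**Conclusion.** The point holds in a limited form. As written, the rules let an outcome event, or a mandatory glucose discontinuation, end follow-up before day 28. Amputation after the final visit, its final level and later foot function can be lost, and the primary analysis either carries an early coverage value to day 28 or omits the patient.

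The direction of bias is unknown and depends on which arm has more withdrawals. Under the assumed inputs (carried coverage of 20–60%, surgery rates 10 points apart) the mean coverage difference moves by 2–6 points relative to 0% scoring, and by nothing if the rates are equal. The documents supply neither input, so they do not show that the primary result is in fact compromised.

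It is tempting to set these shifts against the 21-point difference in Sample size {14}. That is not supported: 50% and 71% are effectiveness proportions, whereas the shifts are in mean percentage coverage, for which the article gives no planning mean or standard deviation.

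**What to change.** Reconcile the researcher-decision section, Concomitant care {11d}, Secondary outcomes and Data management {19} so that stopping study treatment does not end follow-up. The clinical rules for stopping treatment stay as they are.

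1. Collect amputation (yes/no and level) and serious adverse events to day 28 for all randomised patients unless consent is withdrawn. Use a record check or phone call where a visit is not possible or its date has passed.
2. Report amputation in all randomised patients.
3. Before analysis, prespecify how surgery or amputation on the target ulcer enters the primary outcome, instead of relying on last observation carried forward alone. One example is a sensitivity analysis that scores such patients as failure or worst rank.

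The cost is a small amount of extra data collection and analysis. Trial status gives December 2022 as the expected end of recruitment and the article is dated October 2023, so a change to visits may come too late. Records might still be checked, and items 2 and 3 can be settled at any time before analysis.
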